## Abstract

**Background:**

The integration of artificial intelligence (AI) into health sciences students’ education holds significant importance. The rapid advancement of AI has opened new horizons in scientific writing and has the potential to reshape human-technology interactions. AI in education may impact critical thinking, leading to unintended consequences that need to be addressed. Understanding the implications of AI adoption in education is essential for ensuring its responsible and effective use, empowering health sciences students to navigate AI-driven technologies’ evolving field with essential knowledge and skills.

**Objective:**

This study aims to provide details on the study protocol and the methods used to investigate the usability and efficacy of ChatGPT, a large language model. The primary focus is on assessing its role as a supplementary learning tool for improving learning processes and outcomes among undergraduate health sciences students, with a specific emphasis on chronic diseases.

**Methods:**

This single-blinded, crossover, randomized, controlled trial is part of a broader mixed methods study, and the primary emphasis of this paper is on the quantitative component of the overall research. A total of 50 students will be recruited for this study. The alternative hypothesis posits that there will be a significant difference in learning outcomes and technology usability between students using ChatGPT (group A) and those using standard web-based tools (group B) to access resources and complete assignments. Participants will be allocated to sequence AB or BA in a 1:1 ratio using computer-generated randomization. Both arms include students’ participation in a writing assignment intervention, with a washout period of 21 days between interventions. The primary outcome is the measure of the technology usability and effectiveness of ChatGPT, whereas the secondary outcome is the measure of students’ perceptions and experiences with ChatGPT as a learning tool. Outcome data will be collected up to 24 hours after the interventions.

**Results:**

This study aims to understand the potential benefits and challenges of incorporating AI as an educational tool, particularly in the context of student learning. The findings are expected to identify critical areas that need attention and help educators develop a deeper understanding of AI’s impact on the educational field. By exploring the differences in the usability and efficacy between ChatGPT and conventional web-based tools, this study seeks to inform educators and students on the responsible integration of AI into academic settings, with a specific focus on health sciences education.

**Conclusions:**

By exploring the usability and efficacy of ChatGPT compared with conventional web-based tools, this study seeks to inform educators and students about the responsible integration of AI into academic settings.

**Trial Registration:**

ClinicalTrails.gov NCT05963802; https://clinicaltrials.gov/study/NCT05963802

**International Registered Report Identifier (IRRID):**

PRR1-10.2196/51873

## Introduction

### Background

The integration of artificial intelligence (AI) into the education field has led to many possibilities, benefiting both educators and students [1]. AI takes on various roles as an intelligent tutor, a collaborative learning partner, a valuable tool, and even an adviser in influencing educational policies [2,3]. The multidimensional role of AI in education, as demonstrated by the potential for dynamic and adaptive learning experiences, aligns with ChatGPT’s capacity to operate as a valuable educational tool. ChatGPT is a generative AI that can generate complex answers to questions asked by the user. It has been described as a tool offering numerous benefits in the field of education [4]. It serves as a platform for enhancing students’ writing skills through features such as text completion, translation, and summarization tools. Educators can integrate ChatGPT into their courses to customize the learning journey for their students by considering their preferred learning methods and existing proficiency levels [4].

An exploratory survey examining the use of ChatGPT in various domains, including education, health care, and research, revealed both positive and negative impacts [5]. On the positive side, ChatGPT was found to level the playing field for students facing language challenges, enhance comprehension by providing additional details, and offer valuable assistance in crafting writing assignments. However, the study also uncovered negative consequences, such as the potential for inaccuracies, concerns about replacing hard work with automated solutions, and the possible discouragement of critical thinking skills. In addition, questions remained regarding academic integrity and students’ willingness to disclose their use of ChatGPT. These findings emphasize the need for careful consideration and guidance when integrating AI technologies such as ChatGPT into various fields [5].

It is crucial to acknowledge that integrating AI into education can result in unintended consequences [6]. The use of ChatGPT, while presenting remarkable potential, has sparked discussions regarding its potential negative implications. Concerns have been raised regarding its potential to promote academic dishonesty, stifle creativity, and diminish critical thinking abilities [7]. Numerous legitimate concerns encompass a spectrum of challenges. These include the potential for generating inaccurate content and ethical dilemmas such as the imminent risk of bias, instances of plagiarism, and complex copyright matters [8]. The findings of a systematic review exploring the application of ChatGPT in health care education, research, and practice revealed that ethical concerns were prevalent in 33 out of 60 records. These concerns, particularly the risk of bias and plagiarism, often revolved around data privacy and security issues [8]. This underscores the significance of investigating students’ perceptions of ethics and accountability concerning the use of ChatGPT in health sciences.

Within the health sciences domain, the successful use of AI relies on several key factors. First, usability is paramount. For example, chatbots and AI programs designed to simulate conversations with human users must be user-friendly, ensuring that students, health care professionals, and patients can interact effortlessly. Second, efficiency is critical because these chatbots should streamline processes, reduce workload, and provide rapid and accurate responses [9]. Finally, the overall effectiveness of these chatbots plays a pivotal role, as they need to deliver tangible benefits such as improved patient care, enhanced diagnostic accuracy, and increased efficiency in health care operations. Consequently, the usability, efficiency, and overall effectiveness of chatbots in health sciences are vital aspects that warrant careful consideration and optimization for their successful integration into the field [8].

In this study, the term *usability* is defined as “a quality attribute that assesses how easy user interfaces are to use.” The word *usability* also refers to “methods for improving ease-of-use during the design process” [10]. The 5 components of usability are learnability (how easy is it for users to accomplish basic tasks the first time they encounter the design?); efficiency (once users have learned the design, how quickly can they perform the tasks?); memorability (when users return to the design after a period of not using it, how easily can they reestablish proficiency?); errors (how many errors do users make, how severe are these, and how easily can they recover from them?); and satisfaction (how pleasant is it to use the design?) [10]. The evaluation of ChatGPT’s usability will be conducted in health sciences students, as assessing the usability of this AI holds significance due to the potential impact on adopting this technology in the training of these students.

Over the past few years, extensive research has investigated the usability of ChatGPT across various domains. A study assessing ChatGPT’s usability in formal English language learning revealed promising outcomes. The findings showed that ChatGPT is an effective tool for formal English language education, excelling in various learning tasks encompassing conversation, writing, grammar, and vocabulary enhancement [11]. A systematic mapping study examining the usability of chatbots and human-computer interaction systems examined the field exhaustively, drawing on numerous references. Of the 170 studies that met the inclusion criteria, 21 were primary studies. The authors’ conclusions highlighted the emerging nature of chatbot usability research, which mainly comprises surveys, informal experimental studies, and usability tests. They emphasized the need for more formal experiments to rigorously gauge the user experience, leveraging these findings to design guidelines that prioritize usability [12]. To our knowledge, no randomized controlled trial (RCT) has assessed the usability and students’ perceptions of ChatGPT use within the health sciences.

### Study Objectives

#### Primary Objectives

We aim to explore the usability and effectiveness of ChatGPT compared with conventional web-based tools as a supplementary assistance tool to enhance undergraduate health sciences students’ learning experiences and outcomes.

#### Secondary Objectives

Our secondary objectives are to (1) explore students’ perceptions and experiences with ChatGPT as a learning tool; (2) explore the potential benefits of or barriers to using ChatGPT to improve students’ writing abilities in the health sciences; and (3) investigate students’ perceptions of accountability, ethical considerations, and equity concerns related to the use of AI in education.

### Study Hypotheses

The study’s hypotheses are as follows:

*Null hypothesis:* there is no significant difference in technology usability and learning outcomes between students who use ChatGPT (group A) and those who use conventional web-based tools (group B) for accessing resources and completing assignments.*Alternative hypothesis:* there is a significant difference in technology usability between students who use ChatGPT (group A) and those who use conventional web-based tools (group B) for accessing resources and completing assignments.*Exploratory hypothesis:* the learning outcomes of students who use ChatGPT (group A) will significantly differ from those of students who use conventional web-based tools (group B) for completing their assignments. This hypothesis proposes that the choice of intervention (ChatGPT or conventional web-based tools) may influence the learning outcomes and explore the interaction between usability and learning outcomes.

## Methods

### Study Design

We will use a randomized crossover design to ensure equity in the learning experience for all students. This involves assigning students to use ChatGPT (group A) or conventional web-based learning tools (group B) to access resources and assist them in completing their assignments (Figure 1). To address the potential biases associated with the reporting of results using RCT design, we will adhere to 2 specific guidelines: the CONSORT (Consolidated Standards of Reporting Trials) and its extensions. The CONSORT statement was introduced in 1996 to enhance the quality of clinical trial reporting [13]. However, critics observe that the reporting of crossover trials has been inconsistent and incomplete. To address this issue, the CONSORT 2010 statement was extended to provide recommendations for reporting randomized crossover trials, including a specific checklist [14]. This CONSORT extension for crossover trials includes 14 additional items aimed at improving the reporting of such trials. Furthermore, our report will also draw upon the CONSORT-AI, an extension of the CONSORT 2010 statement published in 2020, which focuses on the evaluation of RCTs involving AI [15].

**Figure 1 figure1:**
[figure not shown]
Crossover randomized controlled trial study design on the usability and efficacy of ChatGPT for health sciences students.

### Setting

This crossover RCT will be conducted on the web and will include health sciences students who are registered in a course on chronic diseases and disability, a third-year undergraduate course at Carleton University in Ottawa, Canada.

Eligible participants will receive comprehensive information about the trial, including the study’s purpose and procedure, through both verbal communication and written materials. To address ethical concerns regarding power dynamics between those responsible for the study and those who may be involved in student teaching and assessment (ie, professors) and students, we opted to involve an individual who is independent of the research team in the recruitment process (ie, a teaching assistant [TA] not involved in other aspects of the study). This decision aims to minimize any potential bias or influence that could arise from direct professor involvement in the recruitment and research. By introducing a TA to be involved in recruitment, we strive to create a more equitable research environment and mitigate any power imbalances that may exist between professors and students. This approach helps ensure that the study is conducted fairly and unbiasedly, fostering a research environment that prioritizes equal opportunities for all participants. Both groups will simultaneously work on an assignment.

### Participants

#### Inclusion Criteria

The inclusion criteria consist of health sciences undergraduate students who are aged ≥18 years and of any gender identity at Carleton University, Canada. They must be registered in a course on chronic diseases and disability during fall of 2023.

Students who responded to the advertisements and consented to participate in the study will be included. Participant recruitment will involve the TA who is not associated with the research project and does not hold any power or authority over the students. The research assistant (RA) will be responsible for overseeing the consent process. They will ensure that informed consent is obtained from the students voluntarily and without undue influence.

#### Exclusion Criteria

Students who do not provide informed consent are not included in the study.

### Recruitment

Recruitment will be conducted in September 2023, followed by interventions and assessments in October and November 2023. All students registered in the course will participate in the learning activities (ie, course assignments) included in this study, as these activities are mandatory for completing the course. They will be asked to give their informed consent for the data generated by their participation in the course assignments to be used for the purposes of the study and for web-based questionnaires to be sent to them to gather information about their learning experience while performing the assignments.

The students will be identified from the class list in Brightspace (Desire2Learn; the digital learning environment of the course), and all students who express their consent will be eligible for inclusion. Upon providing consent, the students will receive an invitation email containing instructions to access and complete the web-based questionnaires through the Qualtrics platform (Qualtrics International Inc). If there is no response within 2 weeks of the initial invitation, a follow-up reminder email will be sent to nonresponding students.

### Sample Size

Recently, Luna et al [16] evaluated the performance of an AI compared with that of a group of physiotherapists in a squat exercise–related quiz and found that the AI demonstrated a sensitivity of 84% in providing correct responses. Assuming a minimum sensitivity of 50% as the null hypothesis, we estimated that 45 participants need to be evaluated to obtain a sample that represents the alternative hypothesis of this study with 90% power and 95% confidence (Fleiss method with continuity correction). Considering the possibility of sample loss from the first to the second intervention, we added an additional 10% added to this sample, totaling 50 students. The sample size was calculated using OpenEpi (version 3.01) [17].

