### Randomization and Allocation Concealment

The participants will be allocated randomly to one of the 2 sequences: ChatGPT (A), followed by conventional web-based tools (B), or conventional web-based tools (B), followed by ChatGPT (A). The allocation of participants into sequences (AB or BA) will be determined through computer-generated randomization in an allocation ratio of 1:1. The research team responsible for analyzing the data will be kept blind to the participants’ group assignments. The research team will generate the allocation sequence, and the TA will enroll the participants and assign them to the intervention. The trial will adhere to established procedures to maintain separation between staff that take outcome measurements and staff that deliver the intervention [13,14].

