### Outcomes and Measurements

The outcome measures will be (1) the usability of the technological tools (ChatGPT or conventional) for completing the assignments (primary outcome), (2) the participants’ perception of these tools as support for learning, and (3) the learning outcomes (secondary outcomes). Outcomes and measurements will be collected at 2 points: at the first follow-up, that is, after the first intervention (experimental or control) in the initial phase, and at the second follow-up, that is, after the second intervention (experimental or control) in the final phase (Figure 1).

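### The 90% power claim rests on an AI's quiz sensitivity (84% vs 50%) in an independent-groups formula, so it is not the power of the SUS comparison

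*Protocol article*

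**What the plan says.** The Sample Size section cites a study in which an AI and physiotherapists took a squat-exercise quiz, and which "found that the AI demonstrated a sensitivity of 84% in providing correct responses". It continues: "Assuming a minimum sensitivity of 50% as the null hypothesis", and concludes that "we estimated that 45 participants need to be evaluated to obtain a sample that represents the alternative hypothesis of this study with 90% power". The method is given as "95% confidence (Fleiss method with continuity correction"), run in OpenEpi. For losses between periods, "we added an additional 10% added to this sample, totaling 50 students".

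The hypothesis to which this power is attached is in Study Hypotheses: "there is a significant difference in technology usability between students who use ChatGPT (group A) and those who use conventional web-based tools (group B"). Outcomes and Measurements names as the first outcome "the usability of the technological tools (ChatGPT or conventional) for completing the assignments (primary outcome"). The Usability section and Table 1 measure it by the SUS, scored 0 to 100. Under Study Design and Randomization and Allocation Concealment, the trial is a crossover: students go to sequence AB or BA by "computer-generated randomization in an allocation ratio of 1:1", and each uses both tools. Data Analysis compares the usability scores with a Wilcoxon test.

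**The concern.** A power figure belongs to one endpoint, one effect size and one test. Here the endpoint in the calculation is the share of quiz questions an AI answers correctly. No participant in this trial has that outcome. The primary outcome is a continuous SUS score, and the learning outcome is a grade from 0 to 100. Nothing in the article links 84% or 50% to either.

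The formula also does not fit the design. It compares two independent groups, whereas each student here supplies a score under both tools. The wording (a sensitivity against a null value) reads like a one-sample test, but the number obtained is not a one-sample size.

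This is the only power statement for the primary hypothesis. If the SUS comparison is not significant, readers will take it that the trial had 90% power to find a relevant difference, when no such difference was ever specified. The Results section also plans to use this trial's effect sizes to size larger trials, so the faulty rationale could be carried forward.

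**Working it through.** **Inputs from the protocol article.** p1 = 0.84, p2 = 0.50, power 90%, confidence 95% (sidedness not stated; two-sided matches), Fleiss method with continuity correction, n = 45, then 10% added to reach 50. All are in Sample Size.

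**Step 1: reproduce the 45.** The Fleiss size per group for two independent proportions, with p̄ = (0.84 + 0.50)/2 = 0.67 and d = 0.34, is

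n = [1.960·√(2·0.67·0.33) + 1.2816·√(0.84·0.16 + 0.50·0.50)]² / 0.34² = (1.3033 + 0.7946)² / 0.1156 = 38.07.

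The continuity correction is n_c = (n/4)·[1 + √(1 + 4/(n·d))]²:

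- from n = 38.07: n_c = 43.76, which rounds up to 44;
- from n first rounded up to 39: n_c = 44.69, which rounds up to 45.

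Both are **per group**, so a parallel comparison would need about 2 × 45 = 90.

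**Step 2: rule out other readings.**

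| Reading of the calculation | n |
|---|---|
| Two independent groups, two-sided, 90%, corrected | 44 to 45 per group |
| Same, uncorrected | 39 per group |
| Same, one-sided, corrected | 37 per group |
| Same, 80% power, two-sided, corrected | 35 per group |
| One sample, 84% vs null 50%, normal approximation | (0.9800 + 0.4698)²/0.1156 = 18.2 |
| One sample, exact binomial | 20 |

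Only the first gives the stated figure. The allowance for losses is consistent: 45 × 1.1 = 49.5 and 45/0.9 = 50.

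**Step 3: what 45 completers give on SUS.** For a two-sided 5% paired t-test with n = 45, the noncentral t distribution gives 90% power at a standardised within-student difference d_z = 0.494. Taking the Wilcoxon signed-rank test's efficiency as 0.955, this becomes 0.494/√0.955 = 0.506. With all 50 students completing, the values are 0.468 and 0.479.

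Converting to SUS points needs the SD of the within-student difference, SD·√(2(1 − ρ)). The article gives neither SD nor ρ. I **assume** SD 12 to 22 and ρ 0 to 0.5. Results are for the Wilcoxon test with n = 45:

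| SUS SD | ρ | SD of difference | Detectable at 90% power (0.506 × SD of difference) | Power, 10 points | Power, 5 points |
|---|---|---|---|---|---|
| 12 | 0.5 | 12.0 | 6.1 | >99% | 76% |
| 12 | 0 | 17.0 | 8.6 | 97% | 47% |
| 15 | 0.5 | 15.0 | 7.6 | 99% | 57% |
| 15 | 0 | 21.2 | 10.7 | 86% | 33% |
| 20 | 0.5 | 20.0 | 10.1 | 89% | 36% |
| 20 | 0 | 28.3 | 14.3 | 62% | 20% |
| 22 | 0.5 | 22.0 | 11.1 | 83% | 31% |
| 22 | 0 | 31.1 | 15.7 | 54% | 18% |

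The detectable difference therefore runs from about 6 to about 16 points, and no single power figure can be stated without choosing the difference, SD and correlation.

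**The case against.** The strongest reply is that no arithmetic is wrong and no shortfall is shown. The Fleiss formula does return 44 to 45, and the step to 50 is consistent. In a crossover, 45 students supply 45 observations per tool, so using a per-group size as the total does not by itself leave the trial short. Forty-five pairs are adequate for a standardised difference of about 0.5. The wide power ranges above come from assumed SDs and correlations. Data collection took place in October and November 2023, so the sample cannot change. All of this stands, and none of it rescues the claim: the article states 90% power for its own hypothesis, and the inputs do not concern that hypothesis.

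A second reply is that the paired reading is inferred. The hypothesis is worded as a comparison between students, Data Analysis promises both within-group and between-group comparisons, and it names a Wilcoxon test without saying signed-rank. That is fair, but in a crossover the paired comparison is the natural one, and under an unpaired reading 84% versus 50% would still not be a SUS effect.

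A third reply is that replacing the derivation with a difference solved back from n would misrepresent how the sample was planned. This is a sound caution about wording, and the fix below respects it.

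Because this is an article, details may sit in a fuller document. Here, however, inputs, method and conclusion are all stated, and further detail could not make the conclusion follow.

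**Conclusion.** The concern holds. The 90% is the power to separate 84% from 50% in two independent groups of about 45 each. It is not the power of the SUS comparison. The defect is in what the calculation is applied to, not in its arithmetic, and it does not show the trial to be underpowered.

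On the real endpoint, 45 completers give 90% power for a standardised within-student difference of 0.49 (paired t) to 0.51 (Wilcoxon). This rests on a two-sided 5% level, a paired analysis and a Wilcoxon efficiency of 0.955. The conversion to SUS points rests additionally on the assumed SD and correlation ranges. It should be corrected before results are interpreted, because it is the only assurance given for the primary hypothesis.

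**What to change.** Withdraw the 84% versus 50% calculation as the justification for power, and with it the 90% claim for the study hypothesis. Replace it with a statement along these lines:

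*Fifty students are to be enrolled, of whom 45 are expected to complete both periods. With a two-sided 5% paired test, 45 completers give 90% power for a standardised within-student difference in SUS of about 0.5.*

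Follow it with the corresponding SUS points under a stated SD and within-student correlation, giving a source for each or showing a range as in the table above. Say openly that this detectable difference is derived from the sample size. If the record of how 45 was reached is kept, add that the calculation does not apply to SUS.

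The cost is one rewritten paragraph. Enrolment, endpoint and analysis are unchanged. The stated power becomes less favourable for small SUS differences.

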### Data Analysis

This study aims to compare the 2 interventions in terms of usability, student perception, and learning outcomes. The crossover design allows for within-group and between-group comparisons, enabling a comprehensive analysis of students’ perceptions of the use of the intervention and its impact on their learning, as well as the effects of the intervention on their learning outcomes.

The use of an identification code will anonymize data. The data set will be exported from the datasheet and imported into the SPSS software (version 28.0; IBM Corp) for Mac, where the data will be subjected to analysis with a confidence level of 95%. Descriptive statistics, including the calculation of frequencies, will be performed on the sociodemographic variables of the students. The usability scale and grades at each assessment time will be summarized using mean and SD. The nonparametric Wilcoxon test will be used to compare the differences between these variables.

The frequencies, means, and SDs of each item of the SUS scale will be calculated and compared using the McNemar or chi-square and Wilcoxon tests, respectively. In addition, the usability scores and the grades of each group will be correlated using Spearman correlation.

For the analysis of perception and usability outcomes, we will use the Spearman correlation coefficient to assess the relationship between the 2 scales. This statistical approach was chosen to measure the strength and direction of the associations between variables when the data may not conform to a linear pattern. Using the Spearman correlation coefficient, we aim to better understand how perceptions and usability factors are interrelated, providing a robust basis for our research findings and conclusions. To assess the internal consistency of the scales, Cronbach α coefficient will be calculated for both constructs and for each individual item.

To categorize the students into groups of low and high performance (using a cut-off value of 80) and classify the SUS scale into high and low usability groups (with a cut-off value of 50), appropriate statistical tests will be applied. Specifically, Fisher exact test or Pearson chi-square test will investigate the associations between the categorized scales and sociodemographic characteristics.

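### Possible loss between periods is met only by adding students, while the named Wilcoxon comparison, read as paired, drops students who have only a first-period SUS and ignores period

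*Protocol article*

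**What the plan says.** Protocol article, Sample Size: "we estimated that 45 participants need to be evaluated". The section then raises this figure to a total of 50 and gives the reason: "Considering the possibility of sample loss from the first to the second intervention, we added an additional 10" per cent. This enlargement is the only place where the article deals with such loss.

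Protocol article, Data Analysis: SUS and grades are summarised at each assessment, and then "The nonparametric Wilcoxon test will be used to compare the differences between these variables". Neither signed-rank nor rank-sum is specified, and no period or sequence term is named. SUS items are compared with McNemar or chi-square and with Wilcoxon tests. The same section says that the design permits comparisons both within and between groups.

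Outcomes and Measurements makes usability the primary outcome, measured once after each period. Perception of Ethics and Accountability says that two measurements allow change to be followed within a participant who switches tools.

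Recruitment: "All students registered in the course will participate in the learning activities (ie, course assignments) included in this study". The coursework is compulsory but answering the questionnaires is not. Loss would therefore fall mainly on the SUS and the perception survey.

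**The concern.** A student who returns the first SUS and then stops has given a valid score for a randomised tool. A signed-rank test cannot use it, because there is no second score to subtract. Which score is missing depends on sequence: an AB student who stops lacks the SUS for conventional tools, and a BA student who stops lacks the SUS for ChatGPT.

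If those who stop are mainly students who rated the first tool poorly, the remaining pairs have first scores that are too high on average, and their second scores fall back toward the mean. In AB this favours ChatGPT; in BA it favours conventional tools. With equal loss in the two sequences the two shifts cancel; with unequal loss they do not.

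There is a second route. With unequal numbers of pairs, a period effect no longer cancels in an analysis that has no period term. A period effect is possible here because the second assignment uses a different topic (Washout Period), although the team aimed for similar complexity.

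What is at stake is the estimate and the false-positive rate for the primary outcome.

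**Working it through.** **1. The plan's own figures.** Inputs from Sample Size are 84% ("found that the AI demonstrated a sensitivity of 84% in providing correct responses"), 50% ("Assuming a minimum sensitivity of 50% as the null hypothesis") and "with 90% power and 95% confidence (Fleiss method with continuity correction"). Two-sided testing is assumed. The Fleiss formula for two independent groups, with mean proportion 0.67, gives

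n = [1.96·√(2·0.67·0.33) + 1.2816·√(0.84·0.16 + 0.50·0.50)]² / 0.34² = (1.303 + 0.795)² / 0.1156 = 38.1, rounded up to 39.

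The continuity correction gives n/4·[1 + √(1 + 4/(n·0.34))]². This is 43.8, so 44, from the unrounded n, and 44.7, so 45, if n is first rounded to 39. The 45 is thus reproduced as a per-group figure. Whether it suits a paired SUS comparison is a separate question and is not pursued here.

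The allowance is 45 × 1.10 = 49.5, or 45/0.90 = 50. If 5 of 50 are lost, 45 pairs remain, so the allowance does its numerical job.

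**2. Bias of the complete-pairs difference.** Assume no true tool difference. Let n_A and n_B be the complete pairs in AB and BA, and π the period effect (second minus first). Let ρ be the within-student correlation, and s_A and s_B the amounts by which the mean first score of retained students exceeds that of all randomised to the sequence. For ChatGPT minus conventional:

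- AB pair, first minus second: expected value (1−ρ)s_A − π
- BA pair, second minus first: expected value π − (1−ρ)s_B
- Bias = [n_A((1−ρ)s_A − π) + n_B(π − (1−ρ)s_B)] / (n_A + n_B)

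**3. Assumed values (none is in the documents).** SD 20, ρ = 0.5, exactly 25 per sequence, 5 students lost. Loss falls mainly on low first scores: students are ranked on first score plus noise of SD 10, which correlates 20/√(400+100) = 0.894 with the score. The SE with 45 pairs is 20·√(2·0.5)/√45 = 2.98.

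**4. Numbers put in.** For the lowest fraction f lost, s = 20 × 0.894 × φ(z_f)/(1−f).

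- *Random loss, all 5 in AB:* s = 0, so bias = (25−20)π/45 = π/9. This is 0 without a period effect and 1.1 points for π = 10.
- *Score-related loss, 5 v 0:* s_A = 17.9 × 0.280/0.80 = 6.3; bias = 20·0.5·6.3/45 = 1.4. With π = 10 add 1.1, giving 2.5.
- *4 v 1:* s_A = 5.18, s_B = 1.61; bias = (21·0.5·5.18 − 24·0.5·1.61)/45 = 0.78.
- *3 v 2:* s_A = 4.06, s_B = 2.89; bias = (22·0.5·4.06 − 23·0.5·2.89)/45 = 0.26.

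**5. Simulation under the same assumptions**

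| Loss (AB v BA) | Period effect | Complete-pairs bias | Signed-rank type I error |
|---|---|---|---|
| 3 v 2 | 0 | 0.2 to 0.3 | about 5% |
| 4 v 1 | 0 | 0.6 to 0.8 | about 6% |
| 5 v 0 | 0 | 1.3 | about 7% |
| 5 v 0 | 10 | 2.5 | about 10% |

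The sign reverses if the losses fall in BA. A period-adjusted likelihood analysis of all observed scores (generalised least squares with known covariance) stayed within about 0.1 of zero, with practically the same SE.

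**6. Sensitivity.** If exactly the 5 lowest scorers in one sequence are lost, the bias is 2.4, 1.5 and 0.6 points at correlation 0.2, 0.5 and 0.8. With a 10-point period effect it is 3.5, 2.6 and 1.7. Adding period while still using only complete pairs removes the bias from random loss but leaves about 1.7 points at correlation 0.5 under this mechanism. The single-period scores have to be kept as well.

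**The case against.** Four arguments stand against the point, and each has some force.

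**It is only silence on missing data.** An article may leave that to a fuller document, and its absence would be no finding. That is correct. The point therefore rests on the test the article does name, set beside a loss it foresees.

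**The paired reading is an inference.** A reader might conclude that the plan tests paired differences and nothing else. The text does not go that far: the type of Wilcoxon test is open, chi-square is unpaired, and between-group comparisons are mentioned. Signed-rank is still the natural reading in a crossover, beside McNemar and the stated interest in within-participant change. A rank-sum test would keep single scores but treat two scores from one student as independent.

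**Unequal loss is neither predicted nor sufficient.** The text speaks of a possibility of loss, so it should not be read as a forecast of 10%. Unequal loss alone does not bias the paired difference; it must also be related to outcome or meet an ignored period effect. If 5 losses were unrelated to sequence, all would fall in one sequence with probability 2·C(25,5)/C(50,5) = 0.05. A reminder e-mail, a 2-minute SUS and a gift-card drawing should limit loss. On the other side, the protocol expects SUS to favour ChatGPT. It also places a survey of about 10 minutes after ChatGPT use, so the two sequences may carry different burdens in the first period.

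**The remedy is favoured by the simulation.** Loss there depends only on observed first scores, and the covariance is taken as known. If students stop because of the second tool or assignment, protection is not assured. This stands and is stated as the cost of the fix.

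A reader might also infer that survey non-responders would lose their grades from the analysis. The protocol does not say so: Intervention and Measurement has the participants' grades collected with no condition on answering surveys.

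**Conclusion.** The point holds in conditional form. Adding 10% protects the number of pairs, not the validity of their comparison. The named test, if paired, discards first-period scores already in hand and takes no account of period.

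The expected size is modest. Under the assumptions in the working, the adverse case of all 5 mainly low-scoring losses in one sequence gives about 1.3 SUS points, or 1.3/2.98 = 0.44 SE, with type I error near 7%. A 10-point period effect raises this to about 2.5 points (0.84 SE) and about 10%. More even splits without a period effect give under 1 point. SD, correlation, period effect and loss mechanism are all assumed, and the documents do not show that such loss will occur. The case for change is that the primary outcome is exposed and that the alternative removes the bias in these scenarios with no loss of precision.

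**What to change.** In Data Analysis, make the main SUS comparison a linear mixed model with tool and period as fixed effects and student as a random effect. Include every randomised, consenting student with at least one SUS. Report the tool difference with its 95% confidence interval. Name the Wilcoxon test as signed-rank and keep it, on complete pairs, as a sensitivity analysis. Report the number with a first SUS only, a second SUS only and both, by sequence.

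The cost is a change of analysis wording and a standard SPSS procedure; no new data or participants are needed. The downside is reliance on a model that assumes missing second scores are explained by the observed first score and sequence. The signed-rank result and the loss by sequence let readers judge how much depends on that. Because Results says that data collection has already taken place, the change should be dated and, if still possible, made before the scores are compared by tool.
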